### **5.1 Serious adverse event (SAE)**

Results (defined above) that meet the criteria for a SAE will not be reported as a SAE, but as outcomes. A SAE is defined as any AE that results in death, is immediately life-threatening, results in persistent or significant deficiency/disability, requires or prolongates the patient's hospitalization, is a congenital anomaly/birth defect, or should be considered serious by any other reason if it is an important medical event when based on proper medical judgment that could jeopardize the patient and may require medical or surgical intervention to prevent one of the other outcomes listed in the definitions above.

The intensity of the AE should be judged based on the following:

- Mild: Awareness of signs or symptoms that are easily tolerated
- Moderate: Sufficient discomfort to cause interference with usual activity
- Severe: Disabling or causing inability to work or perform usual activities.

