## **4.1 ENDPOINTS**

### **4.1.1 Primary endpoint**

Hierarchical combined endpoint of death, acute myocardial infarction, stroke, hospitalization for unstable angina, hospitalization for heart failure, emergency coronary revascularization or hospitalization for respiratory infections.

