## 4.3 Exploratory endpoints

Occurrence of local and systemic adverse events at 7 and 28 days after vaccination. Occurrence of serious adverse events related to vaccination and serious adverse events within 12 months; Occurrence of the primary endpoint between treatment groups within 45 days of randomization; Vaccine antigen responses  $\geq 4$  times baseline by hemagglutination inhibition test.

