### **5.2 Causal relation of the adverse event**

Medical judgment should be used to determine the relation, considering all relevant factors, including reaction pattern, temporal relation, withdrawal or reintroduction of study drug. Only unexpected and previously unreported serious adverse events believed to have a reasonable level of certainty to be related to study medication need to be immediately reported (i.e., within 24 hours of awareness of the event) to the VIP-ACS Project Office. For such events, the research team must complete a SAE CRF and immediately enter it into the e-CRF. The VIP-ACS Project Office will then

inform ANVISA (Brazilian Health Surveillance Agency) in a timely manner in accordance with the SAE Management Plan.

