## 5. ANALYSIS

### 5.1. Outcome definitions

Any suspected cardiovascular event suggestive of an endpoint as well as all deaths were submitted to the blind independent Clinical Events Committee (CEC). The CEC reviewed the data of the reported cases in a blinded manner for adjudication purpose and validate if the event should be considered as an endpoint. Cardiovascular and respiratory events adjudicated and validated by the CEC will be used for the analyses.

Events that the CEC could not classify as well as suspected event according to investigator but not confirmed by the CEC will not be part of the outcomes. defined in study protocol, the following outcomes will be evaluated:

**Primary efficacy outcome:** A hierarchical outcome consisting of all-cause death, myocardial infarction (MI), stroke, unstable angina, hospitalization for heart failure, urgent coronary revascularization or hospitalization for respiratory infection (excluding COVID-19).

**Key secondary outcome:** A hierarchical outcome consisting of CV death, MI, or stroke.

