#### Safety outcomes:

- Number and percent of unexpected serious adverse events (event that presents immediate risk to life, persistent or significant disability, requiring or prolonging the hospitalization, resulting in congenital anomaly, Guillian Barré syndrome, anaphylactic vaccination reaction, Peripheral Facial Paralysis, encephalitis or myelitis, optic neuritis, Stevens-Johnson syndrome, toxic epidermal necrolysis, anaphylactic vaccination reaction, another unexpected event judged as serious).
- Local and systemic adverse events after vaccination.
- Use of other vaccine than those available in the study (Hepatitis, Trivalent Influenza (Government), Pneumococcal, Yellow fever, Viral triple, DPT Adult, HPV).

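### Protocol 5.1 takes outcomes out of SAE reporting with no exception for those suspected to be vaccine-related, so a reaction that presents only as an endpoint may be missed as an SAE

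*Combined protocol and SAP*

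**What the plan says.** Protocol 5.1 opens with the exemption: "Results (defined above) that meet the criteria for a SAE will not be reported as a SAE, but as outcomes". Its next sentence begins: "A SAE is defined as any AE that results in death, is immediately life-threatening". The two are not reconciled.

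Death is an outcome without restriction of cause. Protocol 4.1.1 gives the primary endpoint as "Hierarchical combined endpoint of death, acute myocardial infarction, stroke", followed by the hospitalisation and revascularisation components. SAP 5.1 words it as "A hierarchical outcome consisting of all-cause death, myocardial infarction (MI), stroke, unstable angina", and so on.

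Three provisions depend on an event being an SAE:

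- Protocol 4.3, exploratory endpoints: "Occurrence of serious adverse events related to vaccination and serious adverse events within 12 months".
- Protocol 5.2 limits the 24-hour report to SAEs that are unexpected, not previously reported and thought related with reasonable certainty. It continues: "For such events, the research team must complete a SAE CRF and immediately enter it into the e-CRF".
- Protocol 5.4 requires the coordinating site to be told of a serious adverse event.

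SAP 5.7 sends SAEs that could be trial endpoints to the efficacy methods. The general criteria for seriousness in the SAP 5.1 safety outcomes read "event that presents immediate risk to life, persistent or significant disability, requiring or prolonging the hospitalization, resulting in congenital anomaly". Death is not named. The same list goes on to name specific reactions, including Guillain-Barré syndrome and anaphylaxis, and ends with a catch-all for other unexpected events judged serious.

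**The concern.** Exempting endpoint events from SAE reporting is normal and sensible in an outcome trial, where most such events reflect the underlying disease. The usual safeguard is an exception for events that the investigator suspects the study product caused. No such exception appears here.

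The intervention is a double vaccine dose given during hospitalisation for an acute coronary syndrome, when deaths and infarctions are expected anyway. If one of them was suspected to be a vaccine reaction, these documents would not require an SAE form or a rapid report. A statement at the end of the trial that few or no fatal vaccine-related SAEs were seen would then be hard to interpret. The efficacy comparison does not fill the gap. It counts from randomisation by assigned arm, and it carries neither relatedness nor time since vaccination.

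**Working it through.** No stated figure is in dispute, so the check follows two kinds of event through the text.

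**Case A: a recognisable reaction that proves fatal (e.g. anaphylaxis).**
1. The death is an outcome (Protocol 4.1.1, SAP 5.1) and is reported as one.
2. The reaction is an adverse event in its own right. Under 5.1 an SAE is an adverse event whose result is death, so the reaction qualifies and the death is its result.
3. SAP 5.1 names anaphylaxis and Guillain-Barré syndrome and does not exclude fatal cases. Filing an SAE is possible.
4. Nothing requires it. There is also some ambiguity: these reactions are described in Protocol 4.4.10, within the section that defines endpoints, so the exemption's reference to what is defined above could be read to reach them.
5. The 24-hour route also requires the event to be unexpected, so a listed reaction could fall outside it for that reason alone.

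**Case B: a suspected reaction that presents only as an endpoint (e.g. sudden death, MI or stroke soon after vaccination).**
1. The event is an outcome. There is no separate reaction to file.
2. The first sentence of 5.1 applies and the event is not reported as an SAE.
3. The 24-hour report (5.2), the notice to the coordinating site (5.4) and the vaccine-related SAE endpoint (4.3) all attach to SAEs, so none is triggered.
4. Adjudication (Protocol 4.4.4) assigns a main cause of death. Its categories are cardiovascular and non-cardiovascular, with no vaccine-related category. A qualifying unexpected death is classed as sudden cardiac death.
5. SAP 5.7 sends the event to the efficacy analysis.

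Case B is the gap.

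**Scale.** The number of endpoint events that would be suspected as vaccine-related is not in the documents. Only the pool from which they would come can be computed, with 900 patients per arm:

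- Deaths: 900 × 7.0% = 63 in controls and 900 × (7.0% − 2.0%) = 45 with the double dose; 63 + 45 = 108.
- Other components, SAP 2.3 rates. Controls: 3.4 + 1.0 + 2.7 + 2.9 + 0.6 + 1.0 = 11.6%, or 104.4 events. Double dose: 11.6 − (0.9 + 0.3 + 0.8 + 0.8 + 0.2 + 0.3) = 8.3%, or 74.7. Sum 179.1.
- Other components, Protocol 6.1 rates (emergency revascularisation 1.0%, heart-failure reduction 0.7%): 12.0% and 12.0 − 3.2 = 8.8%, or 108.0 + 79.2 = 187.2.

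These are all expected endpoint events, and one patient may have several. They do not measure how many are affected. Under the adverse event definition in Protocol 5, control events before the vaccination at about day 30 are not post-vaccine events at all.

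**The case against.** A reader might infer that a fatal vaccine reaction can never enter the SAE data, that the reported count of such events is zero by construction, and that the absence of death from the SAP 5.1 list confirms it. The documents do not support this. Case A shows that a recognisable reaction can be filed while the death counts as an outcome. The SAP list names the main reactions, includes immediate risk to life and a catch-all, and excludes no fatal case. Leaving out the word death is a drafting point.

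Other provisions also count against the strong reading:

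- The judgement of causal relation in the opening sentence of Protocol 5.2 is not tied to the SAE form, so it would be wrong to say that no relatedness judgement is foreseen.
- Protocol Table 2 schedules clinical event evaluation at the 7-day and 28-day contacts after vaccination.
- Every death is adjudicated.
- The monitoring committee sees comparative data by group (Protocol 9.7).
- SAP 5.1 adds an analysis of the primary outcome truncated at 45 days.
- Protocol 5.2 refers to an SAE Management Plan, which was not supplied and may contain the exception.

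Most of this stands as mitigation, but it does not close Case B. Comparative data reviewed at 25%, 50% and 75% of data collection are not rapid reporting of a single case. The 45-day analysis runs from randomisation, not from vaccination. If the SAE Management Plan does hold an exception, 5.1 should cite it, because 5.1 as written says otherwise.

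**Conclusion.** The concern holds in a limited form. Protocol 5.1 exempts every defined outcome, all-cause death included, and neither 5.1 nor 5.2 excepts an outcome suspected to be vaccine-related. A reaction that shows itself only as an endpoint therefore need not be reported as an SAE, and may be missed by the Protocol 4.3 endpoint and the 24-hour route. For a recognisable reaction the weakness is only that filing an SAE is not required.

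The number affected is unknown and probably small; the totals of 108 deaths and roughly 179 to 187 other component events must not be read as its size. The conclusion assumes that no exception exists in the SAE Management Plan. The consequence is for safety reporting and its interpretation. The primary efficacy analysis is not affected.

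**What to change.** 1. **Protocol 5.1.** Reconcile the first two sentences: an outcome that the investigator suspects to be related to the study vaccine is reported both as an outcome and as an SAE under 5.2. If the SAE Management Plan already says so, cite it instead.
2. **Alignment.** Make Protocol 4.3 and SAP 5.7 consistent with that sentence, and name death among the serious criteria in the SAP 5.1 safety outcomes.
3. **SAP 5.7.** Add a descriptive listing, by vaccine received, of deaths and endpoint events within 28 days after vaccination, with relatedness where assessed, and give it to the monitoring committee. Event dates are already collected (SAP 2.5) and the 28-day window already exists.

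The listing must not be used as a between-arm comparison. If the double dose is given on the day of randomisation, its window covers days 0 to 28. A control vaccinated at day 30 has a window from day 30 to day 58 (30 + 28), ending between days 53 and 63 over the ± 5 day allowance. SAP 2.3 itself describes the first 45 days as the time of highest cardiovascular incidence, so the baseline risks differ.

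The cost is a short wording change and a few extra SAE forms. Recruitment was ended at 1,800 patients and SAP version 2.0 is dated 14 March 2022, so the new sentence would not prospectively cover most vaccinations. For patients already vaccinated, sites would have to review relatedness retrospectively for the listed cases.

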### **5.2 Causal relation of the adverse event**

Medical judgment should be used to determine the relation, considering all relevant factors, including reaction pattern, temporal relation, withdrawal or reintroduction of study drug. Only unexpected and previously unreported serious adverse events believed to have a reasonable level of certainty to be related to study medication need to be immediately reported (i.e., within 24 hours of awareness of the event) to the VIP-ACS Project Office. For such events, the research team must complete a SAE CRF and immediately enter it into the e-CRF. The VIP-ACS Project Office will then

inform ANVISA (Brazilian Health Surveillance Agency) in a timely manner in accordance with the SAE Management Plan.

### **5.3 Serious Adverse Event Report**

The investigator is responsible for informing local authorities and ethics committees of any unexpected serious adverse events by local requirements.

### **5.4 Treatment of adverse events**

The treatment of any adverse event will be as identified by local investigators and based on Good Clinical Practice. The identification and therapies adopted must be described in the field specific o vaccination safety and/or in the field of Serious Adverse Events contained in the eCRF. If a serious adverse event occurs, the Study Coordinating Site must be informed.

All concomitant medications, except for vitamins and dietary supplements, must be described in the Booklet and reported in the eCRF. The use of medications for prophylaxis or control of febrile conditions must be included in the eCRF.

## **6. STATISTICAL ANALYSIS**

### **6.1 Sample Size Calculation**

Since the design of the original protocol, the sample size calculation was based on the combined endpoint (MACE) results from a meta-analysis of prospective randomized studies evaluating the effect of influenza vaccines in reducing cardiovascular events after a recent ACS, which revealed a 1-year reduction in relative risk of 36%. The previous version of the protocol considered a conservative event reduction model due

to the use of an active control group, and an event-driven approach, estimating an event rate of 12% per year of the primary endpoint; for a superiority study and a hypothesis of relative risk reduction of 18%, for a statistical power of 90% and a 5% two-sided alpha, 953 events in approximately 9200 patients would be required to complete of the study. However, some facts impacted the VIP-ACS study. With the advent of the COVID-19 pandemic, the number of patients with ACS declined at the investigating sites, and of patients with recruitment potential, most received influenza vaccine with the same strains of the study vaccine, which deemed them ineligible to participate in the study. This fact was relevant as in Brazil the national immunization campaign against influenza was strengthened during the years 2020 and 2021, with the reduction of priority groups and focus on all individuals over 18 years of age.

Another important fact occurred in August 2021, when the IAMI trial results showed that intervention with quadrivalent vaccine versus placebo in patients after ACS provided a 28% reduction in the primary composite endpoint of death from all causes, AMI and stent thrombosis. In addition, pooled data from three previous randomized studies were compiled with IAMI trial data showing a 49% reduction in cardiovascular mortality with influenza vaccine versus placebo, in order to confirm previous findings derived from smaller studies with the same objective.

In this sense, and based on the results of the aforementioned meta-analysis, non-controllable factors (COVID-19) and the findings of the IAMI trial, we recalculated the VIP-ACS sample size using a statistical Win Ratio (WR) approach, for analysis of efficacy of the double-dose influenza vaccine compared to the standard dose vaccine, in which it was estimated that the inclusion of 1800 patients (900 per group) for a WR of 1.41 with a power of 82.6% and an alpha of 5 %. These data were obtained over 10,000 simulations, considering the following event rates in the control group: death, 7.0%; AMI, 3.4%; stroke, 1.0%; hospitalization for unstable angina, 2.7%; hospitalization for heart failure, 2.9%; emergency revascularization, 1.0% and hospitalization for respiratory infections, 1.0%, and assuming a reduction of these events with double-dose vaccine in: death by 2.0%; AMI by 0.9%; Stroke by 0.3%; Hospitalization for unstable

angina by 0.8%; Hospitalization for heart failure by 0.7%; Emergency coronary revascularization by 0.2% and Hospitalizations for respiratory infections by 0.3%.

Considering that the primary endpoint of the VIP-ACS comprises more individual endpoints than the IAMI trial, and from the meta-analysis studies, the sample size calculation proposed to the VIP-ACS to assess possible reductions in hierarchical events of the primary endpoint is comprehensive and conservative to the purpose of the study, and overcomes the external conditions involved in the COVID-19 pandemic.

The analysis of the primary endpoint will exclude hospitalizations for respiratory causes caused by COVID-19. To this end, a sensitivity analysis and other exploratory analysis of the impact of COVID-19 on VIP-ACS events are planned.

## 6.2 Statistical Analysis Plan

Details of the statistical analysis plan are described in a separate document (Statistical Analysis Plan – SAP). Characteristics of the study population will be presented by group and in the total sample. Quantitative variables will be described using mean and standard deviation, median and interquartile range, minimum, maximum and number of valid observations. Qualitative variables will be presented by absolute (number of patients) and relative (percentages) frequencies. Statistical tests will not be performed to compare baseline characteristics between study groups.

The primary endpoint will be analyzed by the statistic called Win Ratio proposed by Pocock et al., (2012). The primary hypothesis will be defined as:

H0:  $\Psi=1$  (win ratio = 1): The ratio of the total winning comparisons between the double-dose influenza vaccine and standard dose influenza vaccine groups is equal.

H1:  $\Psi \neq 1$  (win ratio  $\neq 1$ ): The ratio of the total winning comparisons between the double-dose influenza vaccine and standard dose influenza vaccine groups is different.

By this hierarchical method, all patients in the double-dose influenza vaccine group will be compared with all patients in the standard dose group. Initially, pairs will be compared for time to death truncated at 12 months. If both died, the “winner” of the comparison will be the one with a longer time between the moment of randomization and the date of death. In this same sense, the hierarchy of endpoints that make up the primary endpoint that will be evaluated after death will be AMI, stroke, hospitalization for unstable angina, hospitalization for heart failure, hospitalizations for respiratory causes and emergency coronary revascularization. If the patient is not contacted at the 12-month visit, and the follow-up time for mortality assessment is censored; paired comparisons with this individual will be carried out until the time of censoring. The other tie-breaking criteria for the events that make up the primary endpoint are described in further detail in the study Statistical Analysis Plan – SAP.

It is expected that vital conditions of all patients will be obtained during the 12-month follow-up.

Finally, we defined the test statistic (Win Ratio) as the number of wins of the pairs of each group (double-dose influenza vaccine group and standard dose influenza vaccine group).

The results will be presented with the respective 95% confidence intervals. And the final test will use a significance level of 5%.

Interaction tests will be performed for specific subgroups, including:  $> 60$  vs.  $\leq 60$  years-old; male versus female; ACS presentation (with versus without increase); history vs. no history of AMI; history vs. no history of stroke; history vs. no history of heart failure; previous COVID-19 infection vs. no previous infection; history vs. no history of diabetes. Other prespecified subgroups will be detailed in the SAP.

Proportional hazards regression models for Cox survival analysis will also be performed to calculate the HR and its respective 95% CI in the assessment of the primary

endpoint. The validity of the proportional hazards assumption will be assessed using appropriate methods. If necessary, additional appropriate survival analyses will be performed as sensitivity analyses. The non-parametric Kaplan Meier method will be used to estimate the time to the first event of the primary endpoint. Secondary endpoints will be analyzed in a similar way. Additionally, a cost-effectiveness analysis will be performed using the TreeAge software.

## **7. FOLLOW-UP AND DATA CAPTURE SYSTEM**

### **7.1 Follow-up**

Patients will be followed for 12 months, during which they will have in-person visits upon admission/screening, in the first, sixth and 12th months. If the patient is unable to attend medical visits within the established periods, they will be contacted by telephone or videoconference by the local study teams.

### **7.2 Data Collection System**

The means of data collection for the study are electronic medical records via web using the HIAE Data Management System. The data is entered into the system by the site team. All forms are electronically signed by the principal investigator or designee at the sites. Training and support for using the system will be made available to investigators through the coordinating site.

The aforementioned data collection and management system has been validated by previous studies and is safe and reliable for the VIP-ACS study. System features include patient registration, confidential randomization 24 hours a day, data entry, data cleaning and export for statistical analysis, event adjudication.

All patients included in the study will have their clinical data and information relevant to the study collected by qualified personnel trained for confidentiality of

information and secure storage. Volunteers who, by chance, give up their participation during the study follow-up will have their clinical data regarding the inclusion period until the date of participation withdrawal collected and stored.

HUB investigators will maintain the confidentiality of data and means of accessing the electronic platform, protecting the privacy and confidentiality of information in accordance with local regulatory bodies.

